## **7.2 Screening**

Subjects will be offered a screening visit if they express an interest in participating in the trial. They will be assigned a subject identifier number and provided with and asked to read the subject information sheet at least 24 hours prior to attending for screening. At the screening visit the general process of screening will be outlined and all questions about the screening process and the trial answered. The following general principles will be emphasised:

- Participation in the trial is entirely voluntary
- Refusal to participate involves no penalty or loss of medical benefits
- The subject may withdraw from the trial at any time
- The subject is free to ask questions at any time to allow him or her to understand the purpose of the trial and the procedures involved
- The trial involves administration of a unlicensed vaccine and a bronchoscopy
- There is no direct benefit from participating
- The subject's GP will be contacted to corroborate their medical history if possible

The aims of the trial and all tests to be carried out will be explained by the Investigator or the Clinical Research Nurse. The subject will be given the opportunity to ask about details of the trial, and will then have time to consider whether or not to participate. If they do decide to participate, they will sign and personally date two copies of the consent form, one for them to take away and keep, and one for the Investigator. These forms will also be signed and dated by the Investigator or Clinical Research Nurse.

Having agreed to undergo screening, a baseline medical history (including concomitant medication) and physical examination will be performed. Inclusion and exclusion criteria will be checked using a tabulated format. Demographic and occupational data relating to risk of prior TB exposure will be collected. Vital signs will be checked. Subjects will be counselled by one of the Investigators for HIV, Hepatitis B and Hepatitis C testing. Blood tests as specified in the schedule of procedures will be taken. Urinalysis and a pregnancy test will be performed. Chest x ray and pulmonary function testing will be performed on the same day if possible, or scheduled on a separate visit. The total duration of the screening visit will be approximately two hours.

Subjects will be informed that there may be leftover samples of their blood (after all testing for this trial is completed), and that such samples may be stored up to a maximum of 15 years for possible future research. Samples will be stored in liquid nitrogen storage at the Jenner Institute, University of Oxford under the approved study code "Lab T001: Finding an Immune Correlate of Protection against Tuberculosis' (Berkshire REC Reference Number: 06/Q1602/146). Subjects will be able to decide if they will permit such future use of any leftover samples. If they elect not to permit this, all of those leftover samples will be discarded after the required period of storage to meet Good Clinical Practice (GCP) and regulatory requirements.

The subject's general practitioner will be contacted with the written permission of the subject after satisfactory screening as notification that the subject is taking part in the trial and to ascertain any significant medical history.

### **7.3 Enrolment**

Subjects who fulfil the screening criteria, satisfy all the inclusion criteria, and meet none of the exclusion criteria will be enrolled into the trial and their visits scheduled in the calendar. The ongoing eligibility of the subject will be reviewed on the day of enrolment and any new events, medications, or changes to the screening documents recorded. Subjects will be enrolled on the vaccination visit (day 0). The vaccination visit will last approximately two hours, which includes a 60 minute follow up period in the clinic for observation after vaccination. The bronchoscopy visit (day 7) will last several hours. All other pre-vaccination and follow up visits will last approximately 15 to 30 minutes.

Enrolment should take place no longer than 120 days following the date of screening appointment. If more than 120 days elapse, the screening visit should be repeated in full prior to enrolment.

### **7.4 Safety Review**

There will be a short visit for safety review 2 days following vaccination at which the diary card will be reviewed, pulmonary function test repeated and blood tests repeated.

### **7.5 Follow-up**

The maximum trial duration will be around 6 months after the date of enrolment. Procedures will be performed at the time points indicated in the schedule of procedures (Table 1). Additional procedures or laboratory tests may be performed, at the discretion of the investigators if deemed clinically necessary.

## **8. SAFETY REPORTING**

### **8.1 Definitions**

|                             |                                                                                                                                                                                                                                                                                                                                                                                                                                                                                                                                                                                                           |
|-----------------------------|-----------------------------------------------------------------------------------------------------------------------------------------------------------------------------------------------------------------------------------------------------------------------------------------------------------------------------------------------------------------------------------------------------------------------------------------------------------------------------------------------------------------------------------------------------------------------------------------------------------|
| Adverse Event (AE)          | Any untoward medical occurrence in a participant to whom a medicinal product has been administered, including occurrences which are not necessarily caused by or related to that product.                                                                                                                                                                                                                                                                                                                                                                                                                 |
| Adverse Reaction (AR)       | 
An untoward and unintended response in a participant to an investigational medicinal product which is related to any dose administered to that participant.
 
The phrase "response to an investigational medicinal product" means that a causal relationship between a trial medication and an AE is at least a reasonable possibility, i.e. the relationship cannot be ruled out.
 
All cases judged by either the reporting medically qualified professional or the Sponsor as having a reasonable suspected causal relationship to the trial medication qualify as adverse reactions.
 |
| Serious Adverse Event (SAE) | 
A serious adverse event is any untoward medical occurrence that:
 

• results in death

• is life-threatening

• requires inpatient hospitalisation or prolongation of existing hospitalisation

                                                                                                                                                                                                                                                                                                                                         |

|                                                       |                                                                                                                                                                                                                                                                                                                                                                                                                                                                                                                                                                                                                                  |
|-------------------------------------------------------|----------------------------------------------------------------------------------------------------------------------------------------------------------------------------------------------------------------------------------------------------------------------------------------------------------------------------------------------------------------------------------------------------------------------------------------------------------------------------------------------------------------------------------------------------------------------------------------------------------------------------------|
|                                                       | 
 
• results in persistent or significant disability/incapacity
 
• consists of a congenital anomaly or birth defect.
 
 
Other 'important medical events' may also be considered serious if they jeopardise the participant or require an intervention to prevent one of the above consequences.
 
NOTE: The term "life-threatening" in the definition of "serious" refers to an event in which the participant was at risk of death at the time of the event; it does not refer to an event which hypothetically might have caused death if it were more severe.
 |
| Serious Adverse Reaction (SAR)                        | An adverse event that is both serious and, in the opinion of the reporting Investigator, believed with reasonable probability to be due to one of the trial treatments, based on the information provided.                                                                                                                                                                                                                                                                                                                                                                                                                       |
| Suspected Unexpected Serious Adverse Reaction (SUSAR) | 
A serious adverse reaction, the nature and severity of which is not consistent with the information about the medicinal product in question set out:
 
 
• in the case of a product with a marketing authorisation, in the summary of product characteristics (SmPC) for that product
 
• in the case of any other investigational medicinal product, in the investigator's brochure (IB) relating to the trial in question.
 
                                                                                                                                         |

NB: To avoid confusion or misunderstanding of the difference between the terms "serious" and "severe", the following note of clarification is provided: "Severe" is often used to describe intensity of a specific event, which may be of relatively minor medical significance. "Seriousness" is the regulatory definition supplied above.

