## **4.8 Discontinuation of the trial**

The trial will be discontinued in the event of any of the following:

- New scientific information is published to indicate that subjects in the trial are being exposed to undue risks as a result of administration of the IMP, or as a result of the trial procedures or follow-up schedule.
- Serious concerns about the safety of the IMP arise as a result of one or more vaccine related SAE(s) occurring in the subjects enrolled in this or any other on-going trial of the MVA85A vaccine.
- For any other reason at the discretion of the Chief Investigator.

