## 8.2 Causality Assessment

The Investigator and the Local Safety Monitor both determine causality. It is expected that communication and consultation may occur in the assessment of the causality of AEs. The greatest degree of causal relationship (definite > probable > possible > unlikely related > not related) determined by either the Investigator or Local Safety Monitor after their discussions (and review of the volunteer if necessary) will determine the ultimate classification of the AE. Definite (4), probable (3) and possible (2) are considered to be related. No relationship (0) and unlikely (1) are considered to be unrelated. The following guidelines will be used to assess the relationship of all AEs to the administration of the vaccine, with the premise that all local reactions will be considered causally related to the vaccination:

0 = No relationship:

- No temporal relationship to vaccine; and
- Alternate aetiology (clinical state, environmental or other interventions); and
- Does not follow known pattern of response to the vaccine

1 = Unlikely relationship:

- Unlikely temporal relationship to vaccine; and
- Alternate aetiology likely (clinical state, environmental or other interventions); and
- Does not follow known typical or plausible pattern of response to the vaccine

2 = Possible relationship:

- Reasonable temporal relationship to vaccine; or
- Event not readily produced by clinical state, environmental or other interventions; or
- Similar pattern of response to that seen with the vaccine

3 = Probable relationship:

- Reasonable temporal relationship to vaccine; and
- Event not readily produced by clinical state, environment, or other interventions or

- Known pattern of response seen with the vaccine
- 4 = Definite relationship:
- Reasonable temporal relationship to vaccine; and
  - Event not readily produced by clinical state, environment, or other interventions; and
  - Known pattern of response seen with the vaccine

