## 8.6 Reporting Procedure for Adverse Events

Adverse events will be recorded in the CRF. Those adverse events likely to be related to the vaccine, whether serious or not, which persist at the end of the trial will be followed up by the Investigator until their complete disappearance. Moreover, any serious adverse event likely to be related to the vaccine and occurring after trial termination should be reported by the Investigator according to the procedure described below.

The outcome of any non-serious adverse event occurring within 30 days post-vaccination or any SAE reported during the entire trial will be assessed as:

- Recovered/resolved
- Not recovered/not resolved
- Recovering/resolving
- Recovered with sequelae/resolved with sequelae
- Fatal

Subjects who have moderate or severe on-going AEs at the completion of the trial will be advised to consult their General Practitioner (National Health Service) if the event is not considered to be related to the vaccine. A follow-up visit will be arranged to manage the problem and to determine the severity and duration of the event, if it is considered to be related to the vaccine. If appropriate, specialist review within the NHS will be arranged.

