## 8. 7 Reporting of Serious Adverse Events

All SAEs will be documented accurately and notification deadlines respected as specified in the site-specific SOP. SAEs will be reported within 24 hours by the Investigator to the Sponsor or person with appropriate responsibility delegated from the Sponsor (Chief Investigator), and to the Local Safety Committee (see section 4.4). This will be performed by emailing an electronic version of the completed SAE Initial Report Form (CCVTM form VC004F1). Any relevant information concerning the SAE that becomes available after the SAE Initial Report Form has been sent (outcome, precise history, results of investigations, copy of hospital report, etc.) will be forwarded in a timely manner using the SAE Update Report Form (CCVTM form VC004F2). The Sponsor, or person with appropriate responsibility delegated from the Sponsor (Chief Investigator/medically qualified investigator), is responsible for commencing, maintaining and completing the SAE Sponsor Report Form (VC004F3). The anonymity of subjects shall be respected when forwarding this information.

SAEs which are not SUSARs will not normally be reported to the EC and MHRA, unless there is a clinically important increase in occurrence rate, an unexpected outcome, or a new event that is likely to affect safety of trial subjects.

In addition to these reporting requirements, the Investigator shall submit once a year throughout the trial, or on request, a safety report to the EC and MHRA (and a copy to the Sponsor).

We will follow every volunteer up for adverse event until their last visit. We will finish collection of AE data at the end of the trial, last volunteer last visit.

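### Section 8 sets inconsistent causality tests for a serious adverse reaction, so an unexpected SAE that is related under 8.2 need not be a SUSAR and can miss the 7/15-day report

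*Protocol*

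**What the plan says.** Section 8.1 (Definitions) sets the threshold for an adverse reaction (AR) low: "a causal relationship between a trial medication and an AE is at least a reasonable possibility, i.e. the relationship cannot be ruled out". It also lets more than one party apply it: "All cases judged by either the reporting medically qualified professional or the Sponsor as having a reasonable suspected causal relationship" qualify.

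The SAR row of the same table uses another threshold and a single assessor. The event must be serious and, "in the opinion of the reporting Investigator, believed with reasonable probability to be due to one of the trial treatments". The SUSAR row then starts from that term: "A serious adverse reaction, the nature and severity of which is not consistent with the information about the medicinal product in question".

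Section 8.2 (Causality Assessment) has the Investigator and the Local Safety Monitor each rate causality on a five-level scale. The higher rating after their discussion is the ultimate classification, and "Definite (4), probable (3) and possible (2) are considered to be related".

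Section 8.8 ties reporting to the EC and MHRA to SUSAR status: 7 days for fatal or life-threatening cases and 15 days for the rest. Section 8.7 adds that "SAEs which are not SUSARs will not normally be reported to the EC and MHRA", subject to three stated exceptions.

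Two other places use relatedness wording that does not match the 8.2 scale. Section 8.6 refers to "any serious adverse event likely to be related to the vaccine and occurring after trial termination" and uses the same 'likely' test for adverse events persisting at the end of the trial. Section 4.8 refers to "one or more vaccine related SAE(s) occurring in the subjects enrolled" without saying how relatedness is decided.

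**The concern.** The definitions differ on two things at once: how strong the causal link must be (possibility against probability) and whose judgement counts (either of two parties against the reporting Investigator alone). The narrowest version sits in the SAR row, and the SUSAR definition, which triggers expedited reporting, inherits it.

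Whether an unexpected SAE goes to the EC and MHRA within 7 or 15 days can therefore depend on which paragraph the site applies. The events affected are the uncertain or disputed ones, for which a rule taking the higher of two ratings is most useful. Safety is the primary objective (section 3), and section 2.1 says this aerosol dose is being used for the first time, so the route to expedited reporting should be unambiguous.

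**Working it through.** No arithmetic applies. The check sets the tests side by side and traces cases through them.

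| Protocol place | Strength of link required | Who decides |
|---|---|---|
| 8.1, AR | reasonable possibility; cannot be ruled out | reporting professional or Sponsor |
| 8.1, SAR | reasonable probability | reporting Investigator |
| 8.1, SUSAR | as SAR, plus unexpected | as SAR |
| 8.2 | possible, probable or definite | higher of Investigator and Local Safety Monitor |
| 8.6 | 'likely'; not a related level on the 8.2 scale | not stated |
| 4.8 | 'vaccine related'; not defined | not stated |

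**Case A: unexpected SAE, final rating 'possible'.** Under 8.2 it is related. It also fits the AR threshold, since the relationship has not been ruled out. But 'possible' is a separate level below 'probable' in 8.2, so it need not amount to reasonable probability. On the literal SAR wording it need not be an SAR. It then need not be a SUSAR, and 8.8 is not triggered.

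**Case B: unexpected SAE, 'unlikely' from the Investigator, 'possible' or 'probable' from the Monitor after discussion.** Under 8.2 the higher rating stands and the event is related. The SAR wording looks only to the reporting Investigator's opinion, which is that the link is unlikely. On the literal wording it is not an SAR, and 8.8 is again not triggered. This holds even if reasonable probability is read generously to include 'possible', because the Monitor's rating has no place in the SAR wording.

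**Case C: unexpected SAE, both assessors 'probable' or 'definite'.** All the definitions agree and 8.8 applies. The conflict is therefore confined to cases like A and B.

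**Could case A arise here?** In 8.2, 'possible' needs any one of three criteria. 'Definite' needs all three, including a known pattern of response to the vaccine, which an event new in nature can hardly show. Section 4.1 places a bronchoscopy one week after each vaccination. A new kind of respiratory event shortly after it could have a reasonable temporal link to the vaccine, yet also be readily explained by the procedure. It would then meet 'possible' but not 'probable'. This shows that the case is plausible; it does not estimate how often it would occur.

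**Inside the 8.1 table itself.** A serious event can meet the AR row (reasonable possibility, or the Sponsor's judgement) and fail the SAR row. On its face, an adverse reaction that is serious need not be a serious adverse reaction.

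**The case against.** The strongest reply is that the protocol can be read without any gap. Section 8.2 says its guidelines apply to all adverse events, which includes serious ones, and that the higher rating is the ultimate classification. The AR row fits 'possible' and gives the Sponsor a say. If a SUSAR is taken to be an AR that is also serious and unexpected, cases A and B both reach expedited reporting. That reading is open. It does not settle the matter, because no passage says that 8.2 or the AR row overrides the SAR row. What is shown is an inconsistency with a possible consequence, not a certain loss of reports.

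The second reply is that other safeguards remain, and this stands:

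- Under 8.7 every SAE, whatever its rating, goes within 24 hours to the Sponsor or its delegate and to the Local Safety Committee.
- Section 8.7 still allows SAEs that are not SUSARs to go to the EC and MHRA if their occurrence rate rises to a clinically important degree, if the outcome is unexpected, or if a new event is likely to affect subjects' safety.
- A yearly safety report (8.7) and the annual DSUR (8.10) also go to those bodies.

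Third, the last paragraph of 8.6 arranges follow-up of ongoing moderate or severe events considered related, which is close to the language of 8.2. That softens the 'likely' wording but leaves the section with two expressions for relatedness.

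A reader might also infer that the SAE bullet in 4.8 is the only way trial data can stop the study. The documents do not support this. That bullet turns on serious safety concerns, which is a judgement, and another bullet lets the Chief Investigator stop for any other reason. Section 4.1 also records that the Group 2 boost was changed because of mild respiratory events, with no SAE test involved.

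**Conclusion.** The inconsistency is real in the current text and should be corrected, but its reach is narrow. What can be missed is the 7- or 15-day report to the EC and MHRA for an unexpected SAE that is rated only 'possible', or that only the Local Safety Monitor rates as related. This rests on reading the SAR row literally and on none of the 8.7 exceptions being invoked.

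No frequency can be attached to it. The documents give no expected SAE rate and no information on how often the two assessors disagree after discussion. Counting combinations of ratings would not supply one, since the combinations are not equally likely.

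Two stronger readings should be set aside. A reader might infer that the SAR wording removes an independent assessor. The protocol gives the Monitor a role in 8.2 but does not call that person independent; the supportable point is that the SAR row omits the second assessor whom 8.2 requires. A reader might also infer that the primary safety result is affected. It is not: the endpoint is all actively and passively collected adverse events, and SAR or SUSAR labels do not change what is collected.

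**What to change.** In 8.1, define a serious adverse reaction as an SAE whose final classification under 8.2 (the higher of the Investigator's and the Local Safety Monitor's ratings) is possible, probable or definite, or which the Sponsor judges to be related. SUSAR then follows as an SAR that is unexpected. This matches the AR definition and keeps the Sponsor's right to classify an event as related.

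In 8.6 and 4.8, state which 8.2 classification 'likely to be related' and 'vaccine related' refer to. The request is only that these passages be reconciled with the scale. Which events are followed up, and what leads to discontinuation, remains for the sponsor and the investigators to decide.

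The cost is a wording amendment and possibly a few more expedited reports.
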